#### Study aim 3. Moderating effects

We will explore the effect of moderating variables (sex, race, sexual orientation, baseline service connection) by examining the interaction between the intervention outcomes and each moderator in predicting outcome slopes in the growth models. The contrast between intervention outcomes will be multiplied by each moderator variable to form an interaction term. Next, the interaction terms will be included in the analyses for Aim 1 for the primary outcome, one at a time, and their strength of association with the outcome slope will be assessed while controlling the direct effects of the predictors on outcome and the direct effect of moderator variables on outcome. If the interaction term is significant, this suggests moderation.

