### Objectives {7}

In summary, this study focuses on reducing suicidal ideation among YEH who are underserved by the services system. Through this study, we will test our strategy for significantly reducing suicidal ideation (primary outcome), substance use, and depressive symptoms (secondary outcomes) as well as reducing risk factors and strengthening protective factors. Our intervention and conceptual model are based upon Beck’s general cognitive theory [18]. Finally, we will rigorously assess acceptability, feasibility, fidelity, and cost to guide future dissemination efforts. Study aims and hypotheses are listed below:

*Specific Aim 1*. Test the effects of outreach-worker delivered CTSP + SAU versus SAU alone on suicidal ideation (primary outcome), substance use, and depressive symptoms (secondary outcomes) at 3, 6, 9, and 12 months.*Hypothesis*. Youth assigned to CTSP + SAU will show statistically significant improvement on the study outcomes over time compared to those assigned to SAU alone.*Specific Aim 2*. Test the mediating relationship between the intervention and primary and secondary outcomes.*Hypothesis 2a*. Cognitive distortions will mediate the treatment effects on outcomes.*Hypothesis 2b*. The relation between cognitive distortions and outcomes will be further mediated by the risk and protective factors. That is, lower cognitive distortions at the 3-month follow-up will be related to higher levels of protective factors and lower levels of risk factors at 6 months, which in turn will be related to reduced suicidal ideation, substance use, and depressive symptoms at the 12-month follow-up.*Specific Aim 3*. Explore how moderators (baseline service connection, sex, race, sexual orientation) affect individual’s response to CTSP.*Specific Aim 4*. Rigorously assess acceptability, feasibility, fidelity, and cost of outreach-worker delivered CTSP using a mixed-methods approach for future adoption studies.

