## Statistical methods

### Statistical methods for primary and secondary outcomes {20a}

Latent growth models (LGM) and mediational models, as described below, will be estimated using MPlus 8 program and evaluated using generally accepted criteria including chi-square, RMSEA, CFI, and SRMR model fit statistics.

#### Study aim 1

The impact of the two study conditions (i.e., CTSP + SAU and SAU alone) on the outcomes will be tested in Aim 1. For suicidal ideation, a latent growth model (LGM) will be applied to the longitudinal data across 5 time points (baseline, 3, 6, 9, 12 months) to estimate the trajectories of change in suicidal ideation over time. Treatment effects on estimated growth parameters, including the intercept (the initial status) and the slope (trends of change over time), will be specifically tested. It is expected that those assigned to CTSP + SAU will show a sharper decrease in suicidal ideation and maintain a lower level following the treatment than those assigned to SAU alone. Similar LGM and follow-up analyses will be conducted on the secondary outcomes, substance use frequency, and depressive symptoms.

#### Study aim 2

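### The Aim 3 interaction is built from intervention outcomes instead of study condition, so as worded it does not test whether the effect of CTSP differs by moderator

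*Protocol article*

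**What the plan says.** The aim is set in Objectives {7}: Specific Aim 3 asks how four baseline factors "affect individual’s response to CTSP".

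The only description of the analysis is in Study aim 3 (Methods for additional analyses {20b}). It proceeds by "examining the interaction between the intervention outcomes and each moderator in predicting outcome slopes in the growth models". The construction rule follows: "The contrast between intervention outcomes will be multiplied by each moderator variable to form an interaction term". The products are added one at a time to the Aim 1 analysis of the primary outcome, while "controlling the direct effects of the predictors on outcome and the direct effect of moderator variables on outcome". The section does not list what these predictors are. It closes with a decision rule: "If the interaction term is significant, this suggests moderation".

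The receiving model is described in {20a}: "The impact of the two study conditions (i.e., CTSP + SAU and SAU alone) on the outcomes will be tested in Aim 1". Its predictor is the two-level study condition, and its dependent quantities are the growth factors of suicidal ideation over five assessments.

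**The concern.** Whether CTSP works differently by sex, race, sexual orientation or service connection is a question about a condition × moderator coefficient. The analysis text names a different component in two consecutive sentences. Read literally, the outcome stands on both sides of the model and randomised condition is missing from the interaction.

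This is the operative text for Aim 3, and it carries a rule for declaring moderation. If followed as written, the published subgroup conclusions would not answer the aim. If the analyst silently substitutes condition, the analysis departs from its published description. The affected factors matter to the design: they are also the balancing factors of the urn randomisation ({16a}), and the sample is recruited half from the drop-in center and half from youth not connected to services ({15}).

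**Working it through.** **No figure to reproduce.** The article gives no power or error rate for Aim 3. The 0.98 in Sample size {14} concerns Aim 1 and does not bear on this point.

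**Step 1: the texts side by side.**
- Aim ({7}): response to CTSP, by moderator.
- Receiving model ({20a}): predictor is study condition.
- Term ({20b}, Study aim 3): contrast between intervention *outcomes* × moderator.

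The third does not fit the first two.

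**Step 2: what each literal reading would do.**

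Inputs from the article: N = 300 at 1:1; five waves; treatment coefficient on the slope 0.20 in size ({14}).

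Assumptions, because the article gives no values: intercept variance 0.25; residual slope variance 0.09 (SD 0.3); error variance 0.5; binary moderator with prevalence 0.5 or 0.3; two-sided 5%; complete data. Each scenario had 2,000 simulated trials.

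Model: Y(t) = i + s·t + e, t = 0,…,4, with s = β·X + γ·X·M + residual (X condition, M moderator). Each person's least-squares slope, a simple stand-in for the latent growth model, was regressed on X, M and the product term. No moderation means γ = 0. The null rows cover β = 0 and −0.20, with a moderator effect on the slope of 0 or −0.20.

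| Product term | Rejection, no moderation | Rejection, true interaction 0.20 / 0.30 / 0.40 |
|---|---|---|
| Condition × M | 0.042–0.056 | 0.644 / 0.940 / 0.994 |
| Own 6-month, 12-month or change score × M, product only | 0.99–1.00 | 1.00 throughout (12-month score) |
| Own baseline score × M, product only | 0.82–0.97 | not informative |
| Own outcome × M, outcome main effect added | 0.043–0.058 | 12-month score 0.060 / 0.082 / 0.092; 12-month change 0.044 / 0.075 / 0.088 |
| Arm-level contrast × M | not estimable | not estimable |

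**Step 3: why the results come out this way.**

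*Product only.* Within an arm and moderator level, the 12-month score and the fitted slope are strongly related under the assumed variances:
- covariance = 4 × 0.09 + (2/10) × 0.5 = 0.46
- variance of the 12-month score = 0.25 + 16 × 0.09 + 0.5 = 2.19
- variance of the fitted slope = 0.09 + 0.5/10 = 0.14
- correlation = 0.46 / √(2.19 × 0.14) = 0.83

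Without a main effect the product absorbs this relation, so it is significant whether or not moderation exists. The baseline-score row is weaker evidence. Its correlation, −0.10 / √(0.75 × 0.14) = −0.31, comes only from the baseline error that the fitted slope shares, which a latent growth model would separate out.

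*Outcome main effect added.* The product now compares the slope-on-outcome coefficient between moderator levels. With slope SD 0.3 in both levels it is 0.46/2.19 = 0.210 in each, so the error rate is nominal. A real condition × moderator effect barely changes that comparison, hence the 4–9% in the last column.

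With unequal slope SDs the coefficients differ without any moderation. At SD 0.6 in one level: (4 × 0.36 + 0.10) / (0.25 + 16 × 0.36 + 0.5) = 1.54/6.51 = 0.237. Simulated false-positive rates for the 12-month score are 0.14, 0.31 and 0.48 at SD 0.4, 0.5 and 0.6 against 0.3.

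*Arm-level contrast.* One number c for the whole trial makes the fourth column c × M, a multiple of the moderator column. The design has rank 3 of 4.

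**The case against.** The strongest reply is that nobody would fit the literal term. It goes into the Aim 1 model, whose predictor is condition. Aim 3 concerns response to CTSP. The section itself distinguishes predictors, moderators and outcome, and a contrast between interventions naturally means a comparison of arms. Replacing *outcomes* with *conditions* repairs both sentences. The aim is also modest: "Explore how moderators (baseline service connection, sex, race, sexual orientation) affect" is the language of exploration, and no power is claimed for it. All of this stands, and it limits the point to a correction of the text.

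A reader might go further than the text allows and infer that the test would report moderation for every factor even when none exists. The documents do not support that as a general statement. The near-100% rejection needs the outcome to enter only through the product. The article also adjusts for the direct effects of predictors it does not list, and this can be read to require an outcome main effect. On that reading the error rate stays near 5% unless slope variances differ by moderator level, and the article says nothing about those variances. If the contrast is an arm-level quantity, there is no test that could give a false positive.

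The reply does not make the wording correct. The wrong component stands in the construction rule as well as in the introductory sentence, and none of the literal readings is a valid test of treatment-effect moderation.

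**Conclusion.** The Aim 3 interaction is mis-specified as written. It conflicts with the stated aim and with the Aim 1 model, and it does not test whether the effect of CTSP differs by moderator. The consequence depends on the reading:
- false positives, if the outcome enters only through the product (0.99–1.00 for follow-up scores) or slope variances differ by moderator level (0.14–0.48 in the cases tried);
- real moderation missed, if an outcome main effect is included (rejection of 0.04–0.09 for interactions of 0.20 to 0.40, against 0.64–0.99 for the correct term);
- no estimate at all, if the contrast is at arm level.

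The rates rest on assumed variances, complete data and per-person slopes in place of the latent growth model. That the literal term is the wrong one does not depend on them. A drafting slip is the probable cause, the aim is exploratory, and the primary comparison is untouched. It should be corrected because the text fixes the analysis and attaches a decision rule to it.

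**What to change.** Replace the two sentences in Study aim 3 with wording such as: *The condition indicator (CTSP + SAU versus SAU alone) will be multiplied by each moderator. The slope growth factor will be regressed on condition, the moderator and their product, one moderator at a time; the coefficient of the product on the slope is the test of moderation.* Naming condition and moderator as the main effects also settles which predictors are adjusted for.

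The cost is two sentences, with no new data and no additional analysis. Regressing the intercept on the product, or reporting the between-arm effect with a confidence interval in each moderator level, would be optional additions and are not needed for the correction.

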#### Study aim 4. Rigorous assessment of acceptability, feasibility, fidelity, and cost of CTSP for future dissemination efforts

We will use a sequential mixed-methods design as described below.

##### Quantitative data analysis

To examine youths’ perceptions of CTSP, descriptive statistics will be used to summarize indicators of fidelity, acceptability, feasibility, and cost. To examine *fidelity*, descriptive statistics will summarize the fidelity coding instrument (CTRS) scores. We will also explore *acceptability* through youth’s satisfaction scores (CSQ) and whether perceptions differ based on service-connection or demographics. Assessment of *feasibility* includes documentation of (1) whether participants were recruited and maintained in the prevention services as proposed, data which can be obtained from RA screening forms and session records (meetings attended), and (2) whether the recruitment timeline proposed, and other intervention procedures can be maintained as proposed. Average start-up and ongoing estimated *cost* of delivering CTSP will be presented.

##### Qualitative analysis

Transcripts will be analyzed iteratively by two independent coders (Drs. [name] and [name]) using a modified grounded theory approach—modified in that we will orient our initial open coding process around what Patton describes as “sensitizing concepts” including issues related to acceptability, appropriateness, and feasibility [69]. NVivo 11 software will be used to organize and code the data.

##### Integrating qualitative and quantitative data analysis

Quantitative findings may be used to inform some of the qualitative data collection. For example, if some youth are found to be less likely to engage in the intervention or services, we will use the qualitative interview as an opportunity to ask youth about their perception of factors that influenced their participation. Data will be used to identify salient contextual features of service delivery that need to be addressed in future implementation efforts.

### Methods in analysis to handle protocol non-adherence and any statistical methods to handle missing data {20c}

#### Follow-up attrition

Potential biases introduced by differential rates of follow-up by study group will be assessed using 2 × 2 chi-square tests at the 3-, 6-, 9-, and 12-month follow-ups (treatment group, 2 levels, attrition yes/no, 2 levels). Systematic attrition related to participant baseline characteristics (e.g., problem severity) also possesses threats to the internal and external validity of the study. Logistic regression will determine if measures of client functioning at baseline predict follow-up status (e.g., lost).

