### Sample size {14}

The power analyses were conducted using the Monte Carlo simulation method [59]. For the LGMs proposed under Aim 1, previous intervention work established a medium to large effect size for treatment differences on suicidal ideation, with *r*s ranging from 0.42 to 0.77 [60] and Cohen’s *d* ranging from 0.64 to 1.03 [61] from 3- to 12-month post-baseline, favoring the cognitive behavioral treatment. Similarly, treatment differences on secondary outcome, depressive symptoms, also have shown medium to large effect sizes, with *d* ranging from 0.39 to 1.24 for depressive symptoms across 6 months [62]. Aim 1 analyses will compare the growth curves of CTSP + SAU to SAU alone. The proposed sample size is 300, assuming an attrition of 10, 15, 15, and 20% at the 3-, 6-, 9-, and 12-month follow-up (Table 2). For the LGMs, under the conditions of continuous outcome variables (e.g., suicidal ideation) and a dichotomous covariate (i.e., two intervention conditions) that has a regression coefficient of 0.20 (medium effect size) for the slope growth factor [59], a sample size of 300 can produce a power of 0.98 to detect the treatment effect on the growth rate of the outcomes. For Aim 2, mediation analyses (path models) are proposed to identify the mechanisms that underlie the treatment effects. Previous clinical trials have reported treatment differences of medium to large (*d* = 0.49 to 0.88) effect sizes for the proposed mediators, such as perceived burdensomeness [61]. Following the three-path mediation model specification suggested by Thoemmes et al. [63], and assuming medium effect sizes for the path coefficients, the proposed sample size can provide sufficient power (0.92) to detect mediation effects.

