
### Plans to promote participant retention and complete follow-up {18b}

One concern when working with YEH is the critical issue of tracking youth for follow-up assessments. Smart and Ogborne [68] in working with YEH suggest the use of outreach workers to maintain contact with those who are lost to follow-up. This proposed project will also utilize the efforts of outreach workers. Extensive locator information will be obtained at the baseline assessment in which youth designate hangout spots in Columbus, as well as collaterals. Each month, the outreach worker will review and update the contact and collateral information which the youth provided. Finally, we have found that YEH who feel connected to staff stay in contact. Also, youth are offered $5 food gift card incentive for attending the intervention sessions.

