#### Missing data

Missing data will be examined to determine if data are missing completely at random (MCAR) or missing at random (MAR). Full information maximum likelihood (FIML) or the multiple imputation (MI) method will be used to estimate missingness and are shown to produce unbiased results. MPlus will be used as it can handle missing data by providing FIML estimation; otherwise, the pattern mixture model framework will be used to conduct data analyses.

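### The attrition checks, as written, do not test whether the arms lose different kinds of youth and have no stated consequence, so FIML is unbiased only under a condition that the protocol leaves out

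*Protocol article*

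**What the plan says.** All references are to the protocol article.

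- **Follow-up attrition, under {20c}.** Two checks are named. First, "Potential biases introduced by differential rates of follow-up by study group will be assessed", by a 2 × 2 chi-square of arm by loss at 3, 6, 9 and 12 months. Second, "Logistic regression will determine if measures of client functioning at baseline predict follow-up status (e.g., lost"). No arm-by-baseline term is named, and no action follows from either result.
- **Missing data, under {20c}.** The missingness mechanism will be examined (MCAR or MAR). Then: "Full information maximum likelihood (FIML) or the multiple imputation (MI) method will be used to estimate missingness and are shown to produce unbiased results". A fallback follows: "otherwise, the pattern mixture model framework will be used to conduct data analyses". Its trigger is not tied to either attrition check.
- **Statistical methods {20a}, aim 1.** The primary outcome is handled as follows: "a latent growth model (LGM) will be applied to the longitudinal data across 5 time points (baseline, 3, 6, 9, 12 months"), with treatment effects on intercept and slope. Baseline SSI-W is therefore inside the model as the first wave. No other baseline measure is named as a covariate or auxiliary variable.
- **Sample size {14}.** The plan is based on N = 300, "assuming an attrition of 10, 15, 15, and 20% at the 3-, 6-, 9-, and 12-month follow-up", not split by arm.
- **Retention {18b}.** The investigators report that "we have found that YEH who feel connected to staff stay in contact".
- **Outreach worker effects, under {20b}.** Here a preliminary check does have a consequence: a significant outreach-worker effect is added as a control variable to the growth and mediation models.

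**The concern.** Attrition biases a randomised contrast when the kind of participant lost differs between arms in a way that the analysis model does not account for. A chi-square of loss by arm sees only the rate. A regression of loss on baseline status without an arm interaction sees only the average association over both arms. If severe youth leave one arm and milder youth leave the other at equal rates, both can look clean.

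The section treats attrition related to baseline characteristics as a threat to internal validity, yet gives the result nowhere to go. The outreach-worker check shows that the protocol states a consequence when it intends one.

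FIML is unbiased when loss is at random given the variables in the likelihood. With condition and five SSI-W waves in the likelihood, loss must depend only on those. If it also depends on something else measured at baseline that carries further information on later SSI-W, the condition fails even though the data to repair it have been collected. At stake is the primary treatment comparison. The bias can go either way, depending on which arm loses which youth.

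**Working it through.** **Plan's own figure.** The attrition section gives no figure. The nearest is power 0.98 for a slope coefficient of 0.20 at N = 300. A linear growth model with five waves, the stated attrition and two-sided 0.05 gives 0.985 with slope variance 0.1 and residual variance 0.5. It gives 0.72 to 0.999 over slope variance 0.05 to 0.3 and residual variance 0.5 to 1.0. The figure is attainable but cannot be confirmed, because the variances are not stated.

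**Inputs.** From the article: 1:1 allocation, N = 300, loss rising to 20% at month 12. Assumed: equal loss per arm, strength of selection (OR 2 to 3 per SD, or 1 logit, which is OR 2.7), growth variances and all correlations.

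**1. What the checks detect** (1,000 trials of N = 300; loss driven by one baseline measure)

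| Loss pattern | 12-month chi-square significant | Logistic without arm term significant | Both clean | Arm-by-baseline term significant |
|---|---|---|---|---|
| No selection | 5% | 5% | 90% | 5% |
| Opposite directions, OR 2 to 3 | 3 to 4% | 6% | 91 to 92% | 99 to 100% |
| One arm only, OR 2 | 4% | 63% | 37% | 61% |
| One arm only, OR 3 | 5% | 91% | 9% | 93% |

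Opposite-direction loss looks to the planned checks like no selection. One-arm loss is often flagged by the logistic regression, but the flag then has no stated use.

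**2. Bias in the growth-model slope effect** (true −0.20, large sample; assumed variances 0.5 intercept, 0.1 slope, 0.5 residual; measure correlates 0.5 with intercept)

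- Driver is baseline SSI-W, opposite directions, OR 2 to 3: +0.0004 to −0.0010, i.e. none.
- Driver outside the model, opposite directions, correlation with slope 0.3 to 0.5: −0.022 to −0.049. That is 0.022/0.20 = 11% to 0.049/0.20 = 25% of the effect.
- Same, correlation with slope 0, OR 3: −0.008 (4%).
- One arm only, correlation 0.5: −0.017 to −0.024 (8 to 12%).
- Same direction in both arms: −0.0003.
- With the measure added to the model, the estimate for these outside drivers is −0.199 to −0.201.

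**3. Bias in the baseline-adjusted 12-month difference** (no true effect; 1 logit per SD in opposite directions; SSI-W waves correlate 0.49; baseline BDI-II correlates 0.56 with baseline SSI-W and r with each later wave)

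The deciding quantity is what BDI-II adds to baseline SSI-W. Its standardised coefficient for a later wave is (r − 0.56 × 0.49)/(1 − 0.56²) = (r − 0.274)/0.686.

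| r | Coefficient | 12-month bias |
|---|---|---|
| 0.56 | 0.286/0.686 = 0.42 | 0.073 SD |
| 0.40 | 0.126/0.686 = 0.18 | about 0.035 SD |
| 0.30 | 0.026/0.686 = 0.04 | about 0.01 SD or less |

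The top row makes baseline depression a better predictor of later SSI-W (0.56) than SSI-W itself (0.49), so it is an upper case. One-arm loss gives 0.016 SD at r = 0.40 and 0.006 SD at r = 0.30. Adding the baseline measure to the likelihood removed the bias in every scenario.

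**4. Effect on the test.** With 0.80 × 150 = 120 completers per arm, SE ≈ √(1 − 0.49²) × √(2/120) = 0.872 × 0.129 = 0.11 SD. A bias of 0.073 SD shifts the test statistic by about 0.65, giving about 10% false positives at a nominal 5%. A bias of 0.035 SD shifts it by 0.31, giving about 6%.

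**The case against.** The strongest reply is that this is silence, not error. The article condenses a fuller plan that is not shown. Auxiliary variables and interaction terms in an attrition diagnostic are commonly settled there. The article does not say that condition is kept out of the logistic regression or that the growth model will contain nothing else. It also offers MI, which can carry baseline variables, and a pattern mixture fallback. This largely stands. It is why the point is an improvement to stated text and not a charge that the primary analysis is invalid. What it does not answer is that the article does state the checks, gives them no consequence, and attaches no condition to its claim of unbiasedness.

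Four stronger readings are tempting and not supported:

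- *Any loss of different kinds of youth passes both checks and biases FIML.* It does not. Loss driven by observed SSI-W gives no bias, and one-arm loss is flagged in 63 to 91% of trials. Passing both checks about nine times in ten needs near-mirror-image selection at equal rates.
- *The protocol suspects depression, substance use or housing as drivers.* It speaks only of problem severity and client functioning. Severity could mean baseline SSI-W, which is already in the model.
- *The retention remark shows that CTSP changes who stays.* The article says that connected youth stay in contact. It does not say that connection differs by arm, and both arms have an advocate for 6 months. If CTSP raised retention overall, the rates would differ and the chi-square tests look for that.
- *The bias is large.* Even 0.07 SD is small beside the d of 0.64 to 1.03 cited under Sample size {14}.

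**Conclusion.** The point holds in a narrow form and is minor. As written, the two checks do not test for arm-specific selection, and neither has a stated route into the growth model. The claim that FIML or MI gives unbiased results is true only if data are missing at random given the variables actually in the model.

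Bias requires two things together: loss that depends differently by arm on a baseline measure outside the SSI-W model, and a measure that predicts later SSI-W beyond the observed SSI-W. The documents show neither to be present, and they do not exclude either. Under that pattern, with 1-logit opposite-direction loss and 20% lost per arm, the 12-month bias is roughly 0.00 to 0.07 SD. It is nil when loss depends only on observed SSI-W and about nil when selection runs the same way in both arms. These sizes rest on correlations and selection strengths that are not in the documents and are illustrative.

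**What to change.** Three changes to the text under {20c}:

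1. Add condition and condition-by-baseline terms to the attrition logistic regression.
2. Whatever the checks show, include a fixed set of baseline measures as auxiliary variables in FIML, or in the imputation model if MI is used, by arm where feasible. BDI-II, Form 90 use and housing days, and service connection are natural choices. Fixing the set in advance avoids letting a significance test decide the primary model.
3. Qualify the statement on unbiasedness: it holds if data are missing at random given the variables in the model.

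The cost is wording and a few lines of Mplus code. All these measures are already collected at baseline. The change has a limit: baseline auxiliary variables do not remove bias from drivers that arise after baseline, such as connection to staff, and the text should say so.
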